**Exercise Training Protocol**

The training regimen for the concurrent training will consist of 36 sessions of individually supervised work, three times a week for 12 weeks on alternating days (Tuesday, Thursday, and Sunday) (APPINDEX VII). Every training session will be conducted under the strict observation of fitness experts. Each 70-minute session had a 5-minute warm-up, a 60-minute main training session (30 aerobic and 30 resistance), and a 5-minute cool-down. We will use the American College of Sports Medicine's recommendation for type II diabetic individuals served as the basis for the exercise programs (ACSM, 2020).

To minimize biased influence during the main training process, a one-week familiarization period will be implemented beforehand. This familiarization will involve easily adjustable intensity aerobic exercises on a treadmill, such as walking and jogging, as well as low-load resistance exercises that participants can perform for 10–15 repetitions without experiencing fatigue.

The RT program focused on the body's major muscle groups in accordance with recommendations from the American Diabetes Association (Sigal et al., 2006). Exercises that will be done include abdominal curl, standing plantar flexion and squatting with body weight and free weights, machine leg press, neutral rowing, machine bicep curl, triceps pulley, and machine bench press (vertical press) exercise using a multi-gym, leg press machine, and dual adjustable pulley (Cybex International, Medway, Massachusetts). They will be performed between 50 to 85 percent of the estimated 1-RM in line with (Liguori & Medicine, 2020; Mager et al., 2008). Workouts using the circuit form of resistance training (RT) will be employed with intervals of 15–20s between sets, consisting of one - three sets of 10-15 repetitions to near fatigue per set with a 30 to 90 seconds break in between to improve muscle strength (Liguori & Medicine, 2020). To ensure steady repetitions throughout the training program, the weight lifted will be increased gradually.

To determine protocol loads, the 1-RM test will be applied by gradually increasing resistance until the volunteer succeeded in performing no more than one repetition. Start with a warm-up that includes a small weight that is roughly 40–60% of the perceived maximum load in order to calculate each individual's 1-RM. To make sure the muscles are prepared for the subsequent section of the test, give everyone a minute to relax after finishing the warm-up. provide the individual 12–15 repetitions after increasing the weight to a moderate load (60–80% of the perceived maximum). This set should be difficult, but not impossible. Rest for one to two minutes after finishing this set.

After establishing a reasonable weight, encourage the subject to do up to 10 repetitions with a 10% increase in load. Allow the individual an additional one to two minutes of break before continuing if they are able to perform ten or more repetitions with the new weight. Keep an eye on the participant throughout this rest period to make sure they aren't exerting themselves excessively. Increase the weight by 10% again and have them try repetition with the larger load if they are able to finish the set of 10 or more reps. After that, the resistance will be gradually raised until the individuals could only complete each exercise nine repetition or less. Reaching the target number of repetitions in between 3 and 6 tries is the aim of increasing the resistance. Three minutes of rest are permit in between each particular exercise, and two minutes will be permitted between each try. Brzycki 1-RM prediction equation(Brzycki, 1993) will then use to estimate the 1-RM based on the resistance and repetitions recorded on the last try. The mathematical expression for the equation is 1RM = W/ [102.78– 2.78(R)]/100, where R is the maximum number of repetitions and W is the weight was using (Abdul-Hameed et al., 2012).

The aerobic workout will involve using a Cybex treadmill (Cybex Corporation, Ronkonkoma, New York) (McNamara & Stearne, 2013) at moderate intensity (40–59% HRR) to vigorous intensity (60–89% HRR) (Liguori & Medicine, 2020).

We will use the heart rate reserve (HRR) approach, which is based on the Karvonen formula, to determine the target heart rate (THR) in order to manage the intensity of the exercise (Yabe et al., 2021). This approach is appropriate for a broad spectrum of adult fitness levels (ACSM's, 2013a). The following is the formula:

$$\mathrm{THR}=HR rest + [(HR max - HR rest) \times Intensity]$$

*Equation 6 HRR approach Karvonen target heart rate formula*

Whereas:

- HR max = 220 – age
- RH: expressed the number of beats per minute (bpm) at rest.
- Intensity: the decimal representation of the desired level of exercise intensity (e.g., 0.40 for 40%, 0.60 for 60%).

The Polar H7 heart rate monitor (Polar Electro, Kempele, Finland) (Hernández-Vicente et al., 2021) will be used to continually track the participants' target heart rates as they exercise. To giving real-time feedback, this device makes sure that the intensity of the workout stays within the predetermined target heart rate range.

There will be resistance and aerobic workouts within the concurrent resistance-aerobic (CRAT) and concurrent aerobic-resistance (CART) groups. The sequence in which the resistance or aerobic components will be done first and second is the only distinction between the two training regimens (CRAT and CRAT). Every training session, there will be a 5-minute recovery and transition period in between the two training programs (aerobic and resistance components).

To ensure the detection of any adverse events, heart rate, blood pressure, and blood glucose levels will be monitored before and after each exercise session, particularly if a medical professional observes unusual or concerning patterns. It would not be possible to incorporate a placebo therapy that mimicked exercise in this investigation (Arora et al., 2023). Rather, a control group will be created in which individuals continue with their regular care regimen while abstaining from any regular exercise program. This makes it possible to compare the impact of the training program with the individuals' current diabetes control techniques.

**Safety considerations**

The safety and well-being of research participants are of paramount importance throughout the study. All procedures will be conducted with strict adherence to ethical standards and institutional guidelines to minimize risk and ensure participant protection. The research protocol includes detailed measures for monitoring, recording, and reporting any adverse events, whether physical, psychological, or social. These events will be promptly addressed and followed up to ensure resolution and participant support.

Participants will be informed of potential risks during the consent process, including the possibility of discomfort or emotional distress, even from seemingly minimal interventions such as questionnaires. Trained personnel will supervise all exercise sessions to reduce the risk of injury, and medical clearance will be obtained before participation. Emergency procedures and referral pathways will be in place should any health concerns arise during the intervention.

Confidentiality and data protection will be rigorously maintained, and participants will have the right to withdraw at any time without penalty. These safeguards aim to uphold the dignity, safety, and autonomy of all individuals involved in the study.

**Follow-up**

The research protocol includes a structured follow-up plan to ensure ongoing participant safety and support beyond the active data collection phase. All participants will be monitored throughout the 12-week intervention period, with additional follow-up extending four weeks post-intervention to identify and address any delayed adverse events or health concerns.

In cases where adverse events occur, participants will receive appropriate medical attention and continued monitoring until resolution. Follow-up procedures include scheduled check-ins via phone or clinic visits, documentation of health status, and referral to healthcare providers when necessary.

This extended follow-up ensures that any physical or psychological effects related to the intervention are responsibly managed, reinforcing the study’s commitment to participant welfare and ethical research conduct.

**Data management and statistical analysis**

All data will be systematically coded and entered into a secure, password-protected database for computer-assisted analysis. Data handling procedures include double-entry verification and regular monitoring to ensure accuracy, completeness, and consistency. Any discrepancies or spurious entries will be flagged and resolved through cross-checking with source documents.

Statistical analysis will be performed using SPSS version 27. The primary analytical approach is Repeated Measures Analysis of Covariance (RM ANCOVA), which allows for the evaluation of time-dependent changes across intervention groups while controlling for dietary practice as a covariate. This adjustment accounts for individual variability in nutritional habits that may influence metabolic outcomes.

The model will assess:

- **Main effects of time** (pre- vs post-intervention),
- **Main effects of group** (CART, CRAT, COT),

Assumptions of normality, homogeneity of variance, and sphericity will be tested prior to analysis. Violations will be corrected using appropriate statistical adjustments (e.g., Greenhouse-Geisser correction). The level of significance is set at *p* < 0.05, and partial eta squared (η²) will be reported to indicate effect sizes.

The sample size of 39 was determined through power analysis, targeting 80% power to detect moderate effect sizes in insulin resistance and cardiovascular outcomes, with a 5% significance level and allowance for 10% attrition.

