**Research protocol: part 1**

**Project summary**

Type II diabetes mellitus (T2DM) is a progressive metabolic disorder associated with impaired glycemic control, insulin resistance, and elevated cardiovascular risk. Exercise is a well-established non-pharmacological therapy; however, the optimal sequencing of aerobic and resistance training in concurrent exercise programs remains unclear. Clarifying whether exercise order influences cardiometabolic adaptations is essential for refining exercise prescriptions in T2DM management.

The objective of this randomized controlled trial is to investigate the effect of exercise sequence on cardiovascular function and biochemical biomarkers in patients with T2DM. Specifically, the study compares the effects of aerobic–resistance versus resistance–aerobic training sequences on insulin resistance, glycemic control, lipid profile, and cardiovascular function.

A total of 39 men and women aged 41–60 years are recruited and randomly allocated into three groups: concurrent aerobic–resistance training (CART), concurrent resistance–aerobic training (CRAT), and a non-exercising control group (COT). Allocation is stratified by age and sex. The intervention spans 12 weeks, with supervised exercise sessions conducted three times per week. In CART, aerobic exercise precedes resistance training, whereas in CRAT, resistance exercise precedes aerobic training. The control group maintains standard care without structured exercise.

The primary outcomes include changes in cardiovascular function and biochemical biomarkers response. Secondary outcomes include anthropometric indices (BMI, body fat percentage, and waist–hip ratio).

This trial is expected to demonstrate that concurrent training improves metabolic and cardiovascular health in T2DM patients, with potential sequence-specific effects. Findings provide practical evidence for optimizing exercise prescriptions and enhancing the clinical management of T2DM

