**Study design**

This study adopts a two-phase sequential research design to investigate the impact of exercise sequence in concurrent training on patients with type II diabetes. Phase I involved conducting a systematic review and meta-analysis titled “Effect of concurrent continuous aerobic and short rest resistance exercise training on metabolic biomarkers in type 2 diabetes patients: a systematic review and meta-analysis.” This review aimed to summarize and synthesize existing evidence on the effects of concurrent training on metabolic outcomes such as HbA1c, insulin resistance, and lipid profile. The review identified both clinical and methodological gaps in the current literature, with a notable lack of evidence on the role of exercise sequence: specifically, whether performing aerobic training before or after resistance training and controlling confounding variable has differential effects on key metabolic and cardiovascular biomarkers in this population.

Building on the findings from the systematic review, Phase II employs a parallel-group randomized controlled trial (RCT) to address the gaps identified. The trial focuses on the sequence of exercise as a potentially important but under-researched variable in concurrent training programs for individuals with type II diabetes. Participants will be randomly allocated in equal numbers to one of three groups: the CART group (Concurrent Aerobic then Resistance Training), the CRAT group (Concurrent Resistance then Aerobic Training), and a wait-list control group (COT). Randomization will follow a 1:1:1 ratio and will be stratified by sex and age, with participants grouped into four age categories: 41–45 years, 46–50 years, 51–55 years, and 56–60 years. To reduce allocation bias, the randomization process will be overseen by the personal trainer and the principal researcher, while outcome assessments will be conducted by independent data collectors blinded to group assignment.

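### The only between-group test listed is a three-level group effect, which answers neither stated question; two planned contrasts on the change from baseline would be a cheap improvement

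*Protocol*

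**What the plan says.** The protocol's section on data management and statistical analysis names repeated measures ANCOVA, with dietary practice as covariate, as the primary approach. It says the method permits "evaluation of time-dependent changes across intervention groups". It then lists what the model will assess: a main effect of time and a main effect of group with levels CART, CRAT and COT. No contrast among the three groups is named.

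Two questions are stated elsewhere. The goals and objectives section makes aerobic–resistance against resistance–aerobic order the primary aim. The project summary adds an expectation about training as such: "This trial is expected to demonstrate that concurrent training improves metabolic and cardiovascular health in T2DM patients", and goes on to mention possible effects of sequence. The exercise training section explains the control arm: it is there to "compare the impact of the training program" with existing diabetes care. The same section says that order is the only difference between the two training regimens.

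On size: "The sample size of 39 was determined through power analysis". The power sought is 80%, at the 5% level, for a moderate effect on insulin resistance and on cardiovascular measures, and one participant in ten is assumed lost. The study design section adds that "Randomization will follow a 1:1:1 ratio", so there are 13 per arm.

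**The concern.** A three-level group effect is a global test. It rejects when any pattern of group means departs from equality, so its p-value belongs neither to the claim that training works nor to the claim that order matters. It can reject when the two orders differ and training has no average benefit over control.

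Because the training arms share the same content, the training-versus-control question can be put to 26 people against 13 in one comparison. The two-df test spends a degree of freedom on the order difference, which is the other question. At stake are a p-value and an interval that match each claim and, under some conditions, power for training against control in a trial of 39.

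**Working it through.** **Inputs.** From the protocol: 39 randomised, 13 per arm, two-sided 5%, 80% power, 10% attrition, one dietary covariate. The effect is described only as "moderate effect sizes". No standardised difference, SD or pre–post correlation is given, so the effect sizes below are assumptions. d is in SDs of the model residual for change.

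**The protocol's own figure.** 39 cannot be reproduced from its stated inputs alone. Assuming Cohen's f = 0.25, two time points and a pre–post correlation r = 0.6, the time-by-group interaction needs 35, and 35/0.9 = 38.9, rounded up to 39. With r = 0.5 it needs 42, and 42/0.9 = 46.7, rounded up to 47. The match is possible but rests on an assumed r.

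**Why rejection is ambiguous.** Take true effects of +0.4, −0.4 and 0 in CART, CRAT and COT. The average training effect is zero, yet the two-df noncentrality is λ = 13 × (0.16 + 0.16) = 4.16, which gives 39.9% power to reject.

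**Power with equal effects.** For the pattern (d, d, 0) the two-df test and the pooled contrast have the same noncentrality, λ = d²/(1/26 + 1/13) = 8.667d². Only the numerator df differ (2 v 1). Error df = 39 − 4 = 35.

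| d | λ | Two-df test, 5% | Pooled contrast, 5% | Gain (points) | Pooled contrast, 2.5% |
|---|---|---|---|---|---|
| 0.5 | 2.167 | 22.5% | 29.9% | 7.4 | 20.6% |
| 0.8 | 5.547 | 51.1% | 62.9% | 11.8 | 51.2% |
| 1.0 | 8.667 | 71.5% | 81.7% | 10.2 | 72.4% |

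With 35 completers and d = 0.8 the two-df test has 46.2% and the pooled contrast 58.0%. If the two-df test has the stated 80% power (d about 1.10 with 39 analysed), the pooled contrast has about 88%, a gain of 8 points. In the f = 0.25, r = 0.6 scenario with 35 evaluable, λ = 35 × 0.0625 × 2/0.4 = 10.94 and power goes from 81.3% to 89.4%, again about 8.

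**Precision.** The standard error is √(1/26 + 1/13) = 0.340 SD pooled, against √(2/13) = 0.392 SD for a 13 v 13 comparison. The ratio is 0.866, so 13% smaller, whatever the effect size.

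**Power with unequal effects.** Two-df λ = 13 × Σ(effect − mean)²; pooled λ = 8.667 × (average training effect)².

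| Effects in the two training arms | Two-df test | Pooled contrast |
|---|---|---|
| 0.8 / 0.6 | 42.8% | 51.8% |
| 0.8 / 0.4 | 39.9% | 40.4% |
| 0.8 / 0.2 | 42.8% | 29.9% |
| 0.8 / 0 | 51.1% | 20.9% |

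Break-even is where the weaker order has about half the effect of the stronger.

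**Order question.** CART − CRAT remains 13 v 13, with about 24% power at a difference of 0.5 and 51% at 0.8.

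**Why on the change.** A group main effect averages pre and post values. With d = 0.8 in baseline SDs and r = 0.5, the post-only effect is halved to 0.4 and the variance of the average is (1 + 0.5)/2 = 0.75. So λ = 0.16/0.75 × 8.667 = 1.85, and the pooled contrast has about 26% power, against 63% on the change.

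**The case against.** Contrasts under a global model are commonly left to the statistical analysis plan. The project management section assigns that plan to the statistician, and it is not shown. This stands: the absence of a contrast is not by itself an error, and the protocol does not exclude one. What remains is that the protocol does list what its model will assess, and the between-group term listed fits neither stated question.

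Training against control is not the primary aim. This also stands, and it is why the order contrast belongs first in the fix.

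A reader might infer that pooling is a free gain of 10 to 12 points. The documents do not support that. They give no numerical effect size, and a gain that large needs d of roughly 0.62 to 1.01 with equal effects in both arms. The trial exists to ask whether the arms differ, and the rationale section cites mechanisms by which they might. Two contrasts at 5% each also carry a chance of at least one false positive near 1 − 0.95² = 9.75% under the global null. Split to 2.5% each, the pooled contrast has about the same power as the two-df test at 5%.

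A reader might also infer that the plan intends CART v COT and CRAT v COT as its follow-up tests. It names none, so the 13% precision figure describes the arms available and does not measure a loss against a stated analysis.

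**Conclusion.** This is a worthwhile low-cost improvement and not a demonstrated error. The firm part needs no assumed effect size: the one between-group test listed does not correspond to the training claim or to the order question, and separate one-df contrasts do.

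The power part is conditional. With 39 analysed, equal effects in both orders and 5% for each contrast, the pooled contrast gains about 7 to 12 points for d from 0.5 to 1.0, and about 8 at the protocol's 80% target. The gain is nil when one order has about half the effect of the other, negative below that, and nil if alpha is split. It would be too strong to say that the trial cannot test training against control as planned, or that pooling strengthens the primary comparison.

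**What to change.** In the statistical analysis section, specify two one-df contrasts on the change from baseline, each reported with a 95% interval:

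- CART − CRAT, for the primary order question.
- (CART + CRAT)/2 − COT, for training against control.

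They are orthogonal with equal arms (1 × ½ + (−1) × ½ + 0 × (−1) = 0), and approximately so after dropout and covariate adjustment. They replace the three-level test. Give CART − COT and CRAT − COT as descriptive estimates. Say whether each contrast is tested at 5% or alpha is split, and why.

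The cost is a short paragraph and a few lines of syntax, with no new participants, visits or data. The text should state the downsides: the pooled contrast estimates the average of the two orders, it loses power if one order has less than about half the effect of the other, its power gain goes if alpha is split, and it adds no power to CART v CRAT.

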**Study goals and objectives**

The primary aim of this study is to evaluate the effects of aerobic–resistance versus resistance–aerobic exercise sequences within concurrent training on cardiovascular function and biochemical biomarkers in patients with Type 2 diabetes, based on the evidence gaps identified in a prior systematic review and meta-analysis.

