The intervention will last for 12 weeks, with participants in the CART and CRAT groups engaging in supervised concurrent training sessions for one hour per day at 5:00 PM on Tuesdays, Thursdays, and Sundays. Although the types of exercises will be identical between the two intervention groups, the order of aerobic and resistance training will differ. The researcher will monitor and compare changes in anthropometric measures, cardiovascular function, and biochemical biomarkers across the groups through pre- and post-intervention assessments. This two-phase design ensures that the RCT is grounded in a comprehensive evidence base and targets specific unanswered questions identified in the literature, thereby enhancing both the scientific rigor and practical relevance of the study.

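### The effects listed for the primary model are the main effects of time and group; neither is a well-targeted test of CART versus CRAT on change, and no such contrast is named

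*Protocol*

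**What the plan says.** The protocol's section on data management and statistical analysis states: "The primary analytical approach is Repeated Measures Analysis of Covariance (RM ANCOVA"). It justifies the model as allowing the "evaluation of time-dependent changes across intervention groups while controlling for dietary practice as a covariate". It then lists what the model will assess, in two bullets: "Main effects of time (pre- vs post-intervention") and "Main effects of group (CART, CRAT, COT"). The second bullet ends in a comma and nothing follows it. No group-by-time term, CART versus CRAT contrast or other pairwise comparison is named there or elsewhere in the protocol.

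The question that the model has to answer is stated in three other places:
- Study goals and objectives: "The primary aim of this study is to evaluate the effects of aerobic–resistance versus resistance–aerobic exercise sequences within concurrent training".
- Project summary: "The primary outcomes include changes in cardiovascular function and biochemical biomarkers response".
- Study design: "The researcher will monitor and compare changes in anthropometric measures, cardiovascular function, and biochemical biomarkers across the groups through pre- and post-intervention assessments".

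**The concern.** With one measurement before and one after the intervention, the randomised effect is the between-arm difference in change, or the between-arm difference after the intervention given the baseline value. Neither listed effect is that quantity.

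- **Time** averages the change over all three arms. It says that participants changed, not that the arms differed.
- **Group** compares each arm's average of pre and post values. Randomisation makes the expected baseline difference zero, so this average contains only half of any post-intervention difference, plus the chance variation of the baseline.
- **Group** is also a joint test of three arms, one of which does not exercise. A significant result does not say whether the two sequences differ.

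The protocol expects its findings to clarify whether order matters and to inform exercise prescription. An analysis that follows the list literally has little chance of detecting a sequence effect on the test it names. If the relevant effect is picked from the output later, the choice is made after the results are seen.

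**Working it through.** **The plan's own figure.** The sample size of 39 cannot be reproduced uniquely, because the protocol gives only a moderate effect, 80% power, 5% significance and 10% attrition, with no numerical effect size, SD or correlation. Take f = 0.25 as moderate (an assumption), with noncentrality 2f²N/(1−r) for group by time and 2f²N/(1+r) for group.
- Group by time needs 36 at r = 0.6, and 36/0.9 = 40 with attrition, close to 39.
- The group main effect needs 81 to 144 before attrition for r from 0 to 0.8.
- At f = 0.40 and r = 0, both effects need 36 (40 with attrition).

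So 39 fits an interaction more readily than the listed group effect, but it does not prove which was meant.

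**Inputs for the comparison of tests.** From the protocol: 39 participants allocated 1:1:1, so n = 13 per arm; two occasions; 5% level, taken as two-sided. Assumed: equal SD of 1 before and after, pre-post correlation r = 0.5 to 0.7, true post-intervention CART-CRAT difference d = 1.0 or 0.5 SD, no dropout, diet covariate ignored.

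**Pairwise CART versus CRAT.** Noncentrality = δ/√(2v/n), with 36 df (35 for the baseline-adjusted analysis).

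| Quantity compared | δ | v |
|---|---|---|
| Pre/post average (behind the group effect) | d/2 | (1+r)/2 |
| Change (group by time) | d | 2(1−r) |
| Post value adjusted for baseline | d | 1−r² |

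For d = 1.0 and r = 0.5:
- average: 0.5/√(2×0.75/13) = 1.47, power 30%;
- change: 1/√(2×1/13) = 2.55, power 70%;
- baseline-adjusted: 1/√(2×0.75/13) = 2.94, power 82%.

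For d = 1.0 and r = 0.7 the noncentralities are 1.38, 3.29 and 3.57, giving 27%, 89% and 93%. For d = 0.5 each noncentrality halves, and power over the same range of r is 10-11%, 24-36% and 30-41%.

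**The listed test itself: the 2-df group effect.** λ = n·Σ(m_j − m̄)²/v, where m_j is half the post-intervention mean of arm j, v = (1+r)/2, and df are 2 and 36. Set CART at 1.0 and CRAT at 0.

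| Position of COT | Σ(m_j − m̄)² | λ (r = 0.5; 0.7) | Power over r 0.5-0.7 |
|---|---|---|---|
| Midway (0.5) | 0.125 | 2.17; 1.91 | 20-23% |
| Equal to CRAT (0) | 0.167 | 2.89; 2.55 | 26-29% |
| 0.5 SD beyond CRAT (−0.5) | 0.292 | 5.06; 4.46 | 42-47% |

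Power for the same sequence effect therefore runs from 20% to 47%, depending on where the control arm lies.

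**The omnibus interaction, with no sequence effect.** Let both exercise arms improve by 0.8 SD and control not change. The mean change is 0.533 and Σ(m_j − m̄)² = 2×0.267² + 0.533² = 0.427. Then λ = 13×0.427/[2(1−r)] = 5.55 at r = 0.5 and 9.24 at r = 0.7. The test is significant in 51% and 75% of trials, wholly because exercise differs from control.

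**The time effect, with no sequence effect.** If both exercise arms improve equally by d and control does not change, the pooled change is 2d/3 with variance 2(1−r)/39. For d = 0.5 and r = 0.5 the noncentrality is 0.333/0.160 = 2.08 (53% significant). For d = 0.8 and r = 0.7 it is 0.533/0.124 = 4.30 (99%).

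**Simulation** (20,000 runs, 13 per arm, r = 0.5). When all three arms improve equally by 0.8 SD, time is significant in 99.8% of trials, group in 4.8% and group by time in 5.2%.

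**The case against.** **The interaction was probably meant.** The stated purpose of the model describes differences in change between groups, the study design section promises to compare changes, and the trailing comma looks like a lost third bullet. This stands as the likely explanation. It does not supply the missing test: a restored group-by-time term would still be a 2-df omnibus test that exercise versus control alone can make significant.

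**The sequence question is not wholly untested.** A reader might infer that the protocol has no test of sequence at all, or an invalid one. The documents do not support that. The group effect contains half of the CART-CRAT difference, and under randomisation it keeps its error rate (4.8% in the simulation above). The fault is dilution and poor targeting.

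**The time effect need not be misused.** A reader might also infer that the investigators would present a significant time effect as a sequence effect. Nothing in the protocol says so, and when two arms truly improve the test is right to detect change. It simply does not bear on the aim.

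**Some of this is analysis-plan detail.** Confidence intervals, units and the order of secondary contrasts can be left to the SAP, and planning to report partial eta squared does not exclude mean differences. That is fair. But the protocol itself chose to list the effects of its primary model, and the list leaves out the one that matches the aim.

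**A 1.0 SD difference flatters the remedy.** This stands. At 0.5 SD, one reading of a moderate effect, even the baseline-adjusted contrast has only 30-41% power.

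**Conclusion.** The concern holds as a mismatch between the primary aim and the effects listed for the primary model. The group effect is a weak, poorly targeted test of CART versus CRAT on change, and the time effect is not a between-arm comparison. At 1.0 SD, a pairwise contrast on the pre/post average has 27-30% power, against 70-89% on change and 82-93% with baseline adjustment. The listed omnibus group test has 20-47%, depending on COT. Effect sizes, correlations and the position of COT are assumptions, since the protocol gives none. The ranking of the three pairwise analyses holds throughout the range shown; the absolute powers do not carry over to other effect sizes. Correcting the list points the analysis at the right question, but does not by itself give adequate power for a moderate sequence effect with 39 participants.

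**What to change.** Replace the two bullets with one named primary analysis, for example:

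> The treatment effect is the between-arm difference in the week-12 value adjusted for the baseline value (ANCOVA, with dietary practice as covariate). The primary contrast is CART minus CRAT, reported as a mean difference with 95% CI; CART versus COT and CRAT versus COT are secondary. The main effects of time and group are not used to infer a treatment or sequence effect.

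If the repeated-measures model is kept, name the CART minus CRAT contrast in change (group by time) as primary instead. The two analyses target the same effect but are not the same test: their variance factors are 1−r² and 2(1−r). The text should therefore choose one, and neither call them equivalent nor leave the choice open.

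The cost is wording only. No extra data are needed, and SPSS, the package already planned, fits either model. If the analysis has already been run, record the change and its date.
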